## Effect variables

### T-cell response

Two 10 mL blood samples will be taken for assessment of T-cell responses (CD4+ and CD45RO+) to DC-TAB and to the unrelated control antigen tetanus toxoid. Peripheral blood samples are to be collected in heparin tubes to prevent blood clotting, and kept at room temperature, also during transport, until they are processed. Samples should be shipped to the regional laboratory by courier, ensuring delivery preferably within 4 h after sampling, but no later than 6 h after sampling.

T-cell responsiveness assays will be initiated on the day of sample collection. Peripheral blood mononuclear cells (PBMC) will be isolated from blood samples within 8 h after sampling, and immediately subjected to an assay for antigen-specific proliferation. The cell culture assay to determine antigen-specific responses of T cells to either DC-TAB itself, or to tetanus toxoid as a control antigen Peripheral mononuclear cells will be isolated from blood samples, labeled with the fluorescent dye carboxyfluorescein succinimidyl ester (CFSE), and placed in culture with antigen at doses known to stimulate maximum proliferative responses. After 9 days, cells will be harvested, additionally stained with fluorescently labeled antibodies to either CD4 (a marker for helper T cells) or CD45RO (a marker for memory T cells of both the CD4 and CD8 lineage), and subjected to flowcytometry. During flowcytometry, cells will be scored for levels of the original CFSE label, and levels of the additional CD4 or CD45RO marker. Since the CFSE label in a mother cell is equally distributed over its resulting daughter cells, proliferated cells are typified by reduced levels of CFSE, especially after several rounds of cell division. Flowcytometry thus allows quantitation of the fraction of either CD4 or CD45RO cells which have proliferated in culture in response to antigen. All data points will be collected at least in triplicate, with each data point being collected using the combined cells of six individual culture wells.

T-cell responses will be assessed by the Central Reference Laboratory for Immunology, at the National Center for Infectious and Parasitic diseases, Sofia, Bulgaria.

### Antibody assessment

To determine antibody levels to CRYAB/DC-TAB, two 1-mL plasma samples will be collected in the course of processing the blood samples which are already drawn for measuring T-cell responses. When peripheral blood mononuclear cells are isolated from the blood samples for the T-cell assay, as described above, two 1-mL plasma samples will become available during the process. These are collected and stored frozen at -20°C. Samples will be shipped for analysis to Delta Crystallon batch-wise every 6 months.

Antibody assays include a quantitation of total serum IgG titers against CRYAB/DC-TAB using a standard ELISA set up, and a bioactivity assay to evaluate neutralizing activity of serum antibodies. This activity will be evaluated by examining the inhibitory effects of serum dilutions on the ability of DC-TAB to induce activation of a specific reporter cell line in culture.

All antibody assessments will be performed by Delta Crystallon BV, Leiden, the Netherlands.

### MRI

Gadolinium brain MRI will be performed at the visits indicated in the schedule of assessment (section 6.5).

A detailed MRI scanning protocol including but not limited to field strength, slice thickness and gap, pixel size, brain coverage, core brain sequences, gadolinium dose and infusion speed and time between gadolinium dosing and post-dose imaging will be prepared prior to start of the study.

All MRI readings will be performed centrally by the VU Medical Center, Amsterdam, The Netherlands.

### Clinical relapse

A confirmed clinical relapse is defined as the occurrence of new symptoms or worsening of previously stable or improving symptoms and signs not associated with fever, lasting more than 24 hours and accompanied by an increase of at least half a point in the EDSS score or 1 point in the score for at least one of the functional systems (excluding the bowel and bladder and mental systems).

Neurologic deterioration that is classified by the treating physician as a relapse but that does not fulfil these criteria will be documented as an unconfirmed clinical relapse.

Clinical relapses may be treated with systemic corticosteroids if deemed in the best interest of the patient. Dose and duration of treatment is at the discretion of the investigator. In case the clinical relapse coincides with the next study drug administration, the investigator will consult with the sponsor’s responsible medical person to determine if and when the next dose may be given.

### EDSS

The Kurtzke Expanded Disability Status Scale (EDSS) is used to quantify disability in multiple sclerosis.

The following functional systems will be assessed and scored according to the EDSS scale (refer to Appendix one for the overall assessment of the EDSS):

- Pyramidal (ability to walk)
- Cerebellar (coordination)
- Brain stem (speech and swallowing)
- Sensory (touch and pain)
- Bowel and bladder functions
- Visual
- Mental
- Other (includes any other neurological findings due to MS)

### MSIS-29

The patient will be asked to fill out the MSIS-29 version 2 questionnaire at the visits indicated in the schedule of assessments (section 6.5) to assess the impact of multiple sclerosis on daily life.

# Study medication

## Identity of the investigational products

Investigational product

Product: DC-TAB

Formulation: solution for intravenous injection

Strength: 12.5 mg/ml

Vial volume: 1 ml

Placebo

Product: PBS

Formulation: solution for intravenous injection

## Drug manufacturing

The study medication is manufactured under supervision of the sponsor by Novozymes, Sweden. Manufacturing operations are in accordance with Good Manufacturing Practice.

All medication used in this study will be prepared and labeled according to the rules of Good Manufacturing Practice, ICH-GCP and local regulatory requirements.

Study medication labeling contains the following items:

- Study number
- Product identification
- Concentration and volume
- Route of administration
- Expiry date
- Batch number
- Sponsor address and telephone number

## Drug storage and stability

The investigational product is to be stored frozen at -20ºC.

Stability studies are currently ongoing. Previous batches indicated that DC-TAB is stable at -20º ± 5º C for at least 66 months, and at 25 ± 2ºC for at least 24 months. DC-TAB can be thawed and re-frozen for storage at -20ºC at least five times.

## Preparation, administration and dosage of treatment

DC-TAB is provided in ready-to-use 1 ml vials containing 12.5 mg/ml DC-TAB. The pharmacy of the unit of an unblinded nurse not involved in the clinical conduct of the study will prepare the syringes according to the treatment assigned to each individual patient (i.e. 7.5, 12.5 and 17.5 mg). PBS will be added until a total volume of 10 ml is obtained (to limit the residual volume of investigational product in the syringe and needle).

Placebo (PBS) will be sourced from a commercial supplier. 10 ml PBS will be prepared in a syringe. In order to maintain the blind, all study drug syringes will be covered using non-transparent foil.

Syringes will be labeled with the patient’s randomization number, patient’s initials, and date and time of preparation of the syringe. After preparation syringes will be stored between +2 and +8ºC in a refrigerator. In order to maintain the blind, the syringes will be covered using non-transparant foil.

Patients will receive the study medication within three hours after preparation as a bolus injection in the arm. Following injection, the intravenous catheter will be flushed with 10 ml PBS.

## Drug accountability

The sponsor or designate will request the investigator or responsible pharmacist to sign a receipt for the study drugs. All study medication supplied for the study should be kept in a locked secure place with appropriate pharmaceutical precautions.

A “Drug Accountability” record should be maintained by the person responsible for dispensing the trial medication to the patient. This should record which supplies are issued to which patients and any drugs returned unused. Details of any supplies that are inadvertently damaged should be given on this record, which will be collected by the monitor at the end of the study.

All unused study medication should be kept and added to the drug accountability record. All study medication in these categories will be inventoried by an unblinded monitor not involved with other monitoring tasks during and at the conclusion of the study. The monitor will arrange for their secure disposal at the end of the study.

The drugs supplied for this study are only intended for use by patients in this study. They must not be diverted for use by others.

# Data handling and record keeping

## Data collection

Data collection is the responsibility of the clinical trial staff at the site under the supervision of the Principal Investigator. During the study, the Investigator must maintain complete and accurate documentation for the study.

Conducting a trial and the related use of CRFs should not detract from the routine data recording in the source documents. It should be clearly marked in the medical records of the patient at the trial site that the patient is participating in a particular clinical trial. Source data must be available to document the existence of the patient and substantiate integrity of trial data collected. Source data must include the original documents related to the trial (e.g. ECG traces, laboratory prints), to the medical treatment and to the history of the patient.

All data obtained in the clinical trial described in this protocol will be transcribed to Case Report Forms (CRFs). All missing data will be explained. CRF items not done will be marked as “ND.” If an item is unknown or not applicable to the specified case, the space in the CRF will be marked “UNK” and “NA”, respectively. Data that has been collected but cannot be retrieved will also be marked “UNK.” All data entries will be made in permanent, black ink.

The CRFs for the recording of trial data for each patient will be presented in a booklet or bundle.

Each CRF must be filled in neatly with a ballpoint pen only. The final authorization of the CRF is considered to be the "End Of Trial" (EOT) form. The PI signs the EOT form to signify review of the booklet and EOT form and to certify them to be complete and accurate.

At each visit of the monitor, the CRFs should be available for review.

The following information should be included in the source medical records:

- demographic data
- medical history
- full physical examination details
- adverse events and concurrent treatment(s)
- ECG traces
- visit dates and dispensing of study medication
- information on the patient’s treatment
- hematology, biochemistry and urinalysis results
- MSIS-29 questionnaire
- EDSS scale

The following information may be recorded directly in the CRF and should be considered as source data:

- vital signs
- body temperature
- brief physical examination conduct
- recording of dates and times of blood sample drawings

## Data management

Data management will be performed by PSI Ltd., Russia.

The completed CRF will be submitted to the clinical data management department of PSI. The data entry will be carried out using ClinTrial^TM^, version 4.7. All data collected will be entered in the database. Two different operators will enter data in duplicate, and control checks between the two databases will be done until 100% concordance is reached.

Queries will be issued, e.g. on missing data, inconsistencies, illegible data, illegal values and unclearly corrected items. Resolution of queries will be implemented in the database. Certain (obvious) errors may be resolved by the assigned data manager in accordance with PSI SOP’s. All other errors will be queried by the data manager and resolved by the investigator.

Errors in the CRF must be corrected by drawing a single thin line with ballpoint pen only, through the incorrect entry and by writing in the new value as close to the original one as possible. Corrections are to be initialed and dated by the person making the correction and, if deemed necessary, the reason for correction must be explained next to the correction made.

## Record keeping

The investigator will maintain a study file, which he/she should use to file the IB, protocol, drug accountability records, correspondence with the IEC/IRB, the sponsor and other study-related documents.

The investigator’s copy of the CRFs, study file, consent forms, drug accountability records and the patient identification list must be kept by the investigator for at least 15 years. These documents should be retained for a longer period, however, if required by the applicable regulatory requirements. It is the responsibility of the sponsor to inform the investigator/institution as to when the documents no longer need to be retained. In addition the investigator must make provision for the patients’ records to be kept for the same period of time.

The sponsor will archive and retain all documents pertaining to the study for at least 15 years after the last approval.

# Statistical analysis and reporting

## Study parameters

### Safety parameters

- Number and frequency of adverse events including local irritability complaints
- ECG parameters
- Clinical chemistry and hematology parameters
- Urinalysis
- Vital signs and body temperature
- MRI signs and symptoms

### Effect parameters and endpoints

Effect parameters

- - Proliferative CD45RO+ (memory) and CD4+ (helper) T-cell response to DC-TAB
  - New or enlarging gadolinium-enhancing lesions on T1-weighted MRI
  - Clinical relapse
  - EDSS
  - MSIS-29
  - Levels of serum antibodies against CRYAB/DC-TAB

Exploratory effect endpoints

- Change in T-cell responses (CD4+ and CD45RO+) to DC-TAB throughout the study
- Cumulative number of new or enlarging gadolinium-enhancing MRI lesions between week 4 and 24, and week 4 and 48 first dose, relative to baseline
- The number of clinical relapses between week 0 and week 24, and week 0 and week 48
- Change in EDSS score between week 0 and week 24, and week 0 and week 48
- Change in MSIS-29 score between week 0 and week 24, and week 0 and week 48
- Change in levels of CRYAB/DC-TAB-reactive serum antibodies
- Change in neutralizing activity of CRYAB-reactive serum antibodies

### Pharmacokinetic parameters

- AUC_0-24h_
- AUC_0-∞_
- C_max_
- t _1/2_
- t _max_
- Kel

## Evaluability of data

All patients who received at least one dose of study medication will be included in the safety analysis.

## Statistical analysis

Statistical analysis will be performed by PSI. A statistical analysis plan will be prepared prior data base lock describing the data analysis in more detail. Deviations from the Statistical Analyses Plan will be justified in the study report. All statistical calculations will be performed using SAS version 9.

A statistical analysis plan will be prepared prior to database lock describing the data analysis in more detail.

### Handling of Missing and Incomplete Data

Handling of missing and incomplete data will be detailed in the statistical analysis plan.

### Safety data

Individual and summary blood pressures, heart rate, respiration rate, body temperature and ECG parameters will be presented using descriptive statistics which include tabular form with mean, median, standard deviation and range (min and max) as appropriate.

Adverse events will be coded by SOC and preferred term according to the current version of the Medical Dictionary for Regulatory Activities (MedDRA). Adverse events will be summarized by number of patients and percentage of patients by treatment group, MedDRA SOC and Preferred Term. Serious AEs, drug-related AEs and serious drug-related AEs will also be summarized.

### Pharmacokinetic data

Plasma concentrations will be listed and summarized by nominal time point, and treatment (number of patients (N), mean, standard deviation, minimum, median maximum, coefficient of variation). Individual and mean plasma concentration vs. time profile plots will be produced for each dose level.

All pharmacokinetic calculations will be done using WinNonlin (version 5.2 or higher). Pharmacokinetic parameters will be listed and summarized by treatment.

Statistical analyses of pharmacokinetic data will include enrolled patients who receive study treatment and complete the study. The AUC_last_, AUC_inf_ and C_max_ parameters will be analyzed both prior to and after natural log transformation, as applicable. The pharmacokinetic parameter estimates will be evaluated by Analysis of Variance.

Details will be described in the statistical analysis plan.

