| **Statistical methods**  **Statistical analysis methods**  The primary analysis will be done on the treatment period, i.e. once all patients completed the 24 week timepoint. An additional analysis will be performed at week 48.  Safety population  The safety population will comprise of all patients who received at least one dose of treatment.  Full analysis population (FAS)  The full analysis set (FAS) consists of all patients who received at least one dose of treatment and in whom at least one effect assessment is available beyond baseline.  Sample size  Since this is the first study in patients with MS the sample size is based on medical and practical grounds rather than statistical grounds.  Safety parameters  No formal statistics will be employed   - Adverse events (AEs) will be coded and presented using MedDRA. The overall incidence, the incidence of related as well as the incidence of serious adverse events (SAEs) will be summarized per dose and by body system in tables. - Local tolerability will be presented by overall incidence by treatment group per symptom. - Vital signs (supine blood pressure and heart rate) and body temperature: Descriptive statistics (n, mean, standard deviation, median, minimum, and maximum) will be provided for blood pressure, heart rate and body temperature and for changes from baseline. - Hematology, biochemistry and urinalysis parameters: Descriptive statistics (n, mean, standard deviation, median, minimum, and maximum) will be provided on values at baseline and all post-dose assessments. Descriptive statistics will be calculated on the change from baseline values. Out-of-normal-range values will be indicated for each parameter. The change in out-of-normal-range values after administration and at follow up versus baseline will be summarized per group by means of shift-tables. - ECG: Descriptive statistics (frequency, mean, standard deviation, median, minimum, and maximum) on ECG parameters will be provided at baseline and at all post-baseline assessments. Changes from baseline values will be calculated and descriptive statistics will be computed. Shift tables will also be provided to indicate changes in ECG parameters over time.   PK parameters  Descriptive statistics (n, mean, standard deviation, median, minimum, and maximum, plus Geometric mean and CV for C_max_ and AUC and the derived parameters) will be provided for the PK parameters.  Evaluations of dose-proportionality and effects of multiple dosing will be performed.  Effect parameters  Descriptive statistics (n, mean, standard deviation, median, minimum, and maximum) at each visit will be provided for all effect parameters and as well as change from baseline (n, mean, standard deviation, median, minimum, and maximum).  A Student’s T-test will be performed to analyze the changes in the absolute percentage of proliferated T-cells and of the cell division index over time.  Details on the analysis methods to be used for other effect parameters will be specified in the statistical analysis plan. | |

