## Clinical data

A phase I, placebo-controlled, double-blind clinical study on the safety, tolerability, pharmacokinetics and T-cell tolerizing effect of DC-TAB in healthy volunteers has been finalized. In this study, the effects have been examined of single i.v. dosing (using 4, 12.5, 25 and 37.5 mg doses) in a first part of the study, and three consecutive daily i.v. doses of DC-TAB (using 10, 25 and 37.5 mg doses) in a second.

Single dose, bolus administration of DC-TAB up to 37.5 mg was well tolerated and safe. In addition, daily dosing of up to 37.5 mg for three consecutive days was well tolerated and safe in healthy volunteers. Following multiple dosing of high concentrations DC-TAB, mild to moderate injection site reactions were observed. The incidence of these reactions was lower when the concentration of DC-TAB in the bolus injections was lowered.

No changes were detected in serum antibody levels against CRYAB over a 28-day period following any of the treatment regimens.

Pharmacokinetic parameters indicate that serum levels of DC-TAB decrease with a half-life of around 60-75 min at all doses tested.

Immunological data indicate a statistically significant reduction in both CD4+ and CD8+ memory (CD45RO^+^) T-cell responses against CRYAB following a single dose level of 12.5 mg, becoming apparent already within 8 days after i.v. administration of DC-TAB. This effect was maintained for at least 28 days. In half of the subjects, the T-cell responses to CRYAB were suppressed to levels considered to reflect non-responsiveness. Antigen-specific T-cell responsiveness (partially) recovers 6-8 months after treatment. These findings are consistent with the notion that i.v. administration of DC-TAB induces antigen-specific inducible regulatory FoxP3+ T cells (iTregs), which functionally suppress the response by other T cells. Consistent with what is known on the dynamics of such a response, the suppressive effect was found to be partially lost after 6-8 months.

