# Investigational plan

## Overall study design and plan – description

This study is a randomized, double-blind, placebo-controlled, exploratory, dose-ranging Phase IIa study to evaluate the safety, tolerability, T-cell tolerance inducing effect, clinical effects, pharmacokinetics, and effects on serum antibodies of human alpha B-crystallin (CRYAB), the active ingredient of DC-TAB.

Patients who fulfill all eligibility criteria will be randomized to one of the treatments, placebo, 7.5 mg DC-TAB, 12.5 mg DC-TAB or 17.5 mg DC-TAB in a 1:1:1:1 fashion. Patients will receive a single i.v. bolus injection treatment which will be repeated twice with 2-month intervals during the 6-month monitoring period. By a single intravenous bolus administration of DC-TAB, a state of T-cell tolerance is expected to be established within days. Each month, T-cell responses to DC-TAB will be assessed (the results of which will be known two weeks after blood sampling). The interval period between treatments may be adjusted in case the duration of the tolerizing effect in patients is different from what is currently expected.

The study consists of two parts, a treatment period of 24 weeks and a follow up period of an additional 24 weeks. Patients will return to the hospital weekly during the first month, and monthly thereafter.

The primary analysis will be performed on the treatment period, i.e. after all patients have completed 24 weeks; an additional analysis will be performed once all patients have completed the study. Patients and site study personnel will remain blinded throughout the study.

After 12 and 24 patients have completed 4 and 12 weeks of follow-up, a partially blinded safety review will be conducted by the DMC to verify safety and adequate tolerization by the intervention in MS patients.

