### Withdrawal of patients

A treatment withdrawal is a patient who stops treatment prematurely (for any reason).

If, during the course of the study, there is deterioration in the patient’s well being or the investigator feels that it is in the patient’s best interest to be stop study treatment, the patient treatment can be discontinued. In case a serious adverse event related to the study medication occurs, the study treatment must be stopped permanently for this patient, unless doing so would harm the patient in the opinion of the investigator.

The patient has the right to stop study treatment or completely withdraw from the study at any time and for any reason.

All patients discontinuing study treatment should have a final visit including at least all safety assessments (see also section 6.3). Reasons for patient withdrawal will be documented in the CRF.

Patients withdrawn or stopping treatment after first administration of study medication will not be replaced. Patients withdrawn prior to first administration of study medication will be replaced.

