## Treatment period (week 0-24)

Patients will be hospitalized the evening or the morning before study drug administration and will be discharged from the hospital 24 hours after dosing.

During hospitalization, patients will undergo a series of assessments (see schedule of assessments, section 6.5). The last available values measured prior to first study drug administration will be considered baseline measurements against which measurements during the treatment period will be compared.

Patients are to refrain from exercise other than the normal daily activities for 24 hours after injection of study medication.

On dosing days study drug administration will take place in the morning upon completion of all necessary pre-dose assessments. The following assessments will be performed: vital signs, ECG, safety biochemistry and haematology, urinalysis and biomarkers. In addition, blood sampling for PK will be performed on the first dosing day. Twenty-four hours after the study drug administration, AEs will be assessed and the patient will be discharged if in good general health. Hereafter the patients will leave the unit.

Patients will return to the hospital for ambulatory visits or hospitalization for the treatment administration visits according to the schedule of assessments, section 6.5.

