## Pharmacokinetics

4 mL blood samples will be taken for assessment of serum concentrations levels of DC-TAB at pre-dose, t=10 minutes, t=20 minutes, t=30 minutes, t=1 hour, t=2 hours, t=4 hours, t=8 hours, t=16 hours and t=24 hours relative to dosing on day 1. Within 2 hours after blood sampling, blood will be centrifuged at 2,000 g for 20 minutes at 4°C. In case a cooled centrifuge is not available, the rotor heads or the centrifuge may be cooled to around 4°C prior to centrifuging. Immediately after centrifugation, serum will be stored in two labelled polypropylene tubes at ≤ -20°C for serum concentration analysis. All serum concentration analyses will be performed according to GLP after the study has been finalized.

DC-TAB in serum samples, stored frozen at -20°C, has been examined for structural stability by informal non-GLP studies, using detectability by a monoclonal antibody in a sandwich ELISA as parameters for integrity. DC-TAB was found to be fully stable under such conditions for a period of at least 6 months.

In ten patients a sample will also be collected at baseline to further investigate the stability of the samples.

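### The PK ANOVA is limited to patients who complete the study, although every PK profile is finished 24 hours after the first dose

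*Protocol*

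**What the plan says.** Section 10.3.3 of the protocol sets the population for the inferential PK work: "Statistical analyses of pharmacokinetic data will include enrolled patients who receive study treatment and complete the study". The next sentences describe that work: AUC and Cmax, untransformed and log-transformed, and an analysis of variance. Earlier in the same section, concentrations and PK parameters are to be listed, plotted and summarised by treatment, with no completion condition attached.

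Section 6.2 places the sampling: "In addition, blood sampling for PK will be performed on the first dosing day". Section 7.3 gives the last time points: "t=8 hours, t=16 hours and t=24 hours relative to dosing on day 1". The schedule in section 6.5 shows no later PK sample. The only other one is a screening sample in ten patients, taken to study sample stability.

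On study length, section 4.1 states: "The study consists of two parts, a treatment period of 24 weeks and a follow up period of an additional 24 weeks". The same section puts the primary analysis after 24 weeks and then says that "an additional analysis will be performed once all patients have completed the study"; the synopsis dates it: "An additional analysis will be performed at week 48".

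On leaving, section 4.4.4 states: "The patient has the right to stop study treatment or completely withdraw from the study at any time and for any reason". It also rules out replacement once a patient has been dosed. Section 6.4 asks patients who merely stop treatment to keep attending the scheduled evaluations.

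**The concern.** The condition for entering the PK analysis is met or failed many months after the data it governs are complete. Whether a patient is still attending at week 48 says nothing about the validity of a concentration profile taken on the first dosing day.

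Two things are at stake. First, precision: PK is a stated secondary objective, the synopsis promises an evaluation of dose proportionality, and each active arm has only 8 patients. Second, selection: completion is a post-dose event, so conditioning on it opens a route by which the analysed patients could differ systematically in exposure from those dosed.

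The PK rule also stands apart from the protocol's other sets. The safety set needs one dose, and the full analysis set needs one dose and one effect assessment beyond baseline. Neither requires completion, and no reason is given for requiring it for PK.

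**Working it through.** The protocol states no dropout rate, power or PK variability, so there is no figure of its own to reproduce beyond 4 arms × 8 = 32 patients, which agrees. Of these, 3 × 8 = 24 are on active drug.

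**Timing.**
- Profile length: 24 h. Study length: 24 + 24 = 48 weeks = 336 days. The profile occupies 1/336 = 0.3% of the study.
- Section 1.5 reports from Phase I that "serum levels of DC-TAB decrease with a half-life of around 60-75 min at all doses tested". So 24 h covers 1440/75 = 19.2 to 1440/60 = 24 half-lives. At 19.2 half-lives the remaining fraction is 2^(−19.2), about 1.7 × 10⁻⁶. On that figure the profile is complete at 24 h.
- If completion were read as week 24 instead of week 48, the mismatch would remain.

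**Profiles lost to the ANOVA.** Assume that a proportion p of patients leave the study fully or are lost to follow-up, independently and equally across arms. The expected loss is 24p. For one arm of 8, P(at least one lost) = 1 − (1 − p)^8 and P(at least two lost) = 1 − (1 − p)^8 − 8p(1 − p)^7. The chance that at least one of the three active arms falls to 6 or fewer is 1 − (1 − P(at least two lost))³.

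| Assumed p | Expected loss of 24 | Given arm loses ≥1 | Given arm loses ≥2 | Any active arm at ≤6 |
|---|---|---|---|---|
| 10% | 2.4 | 1 − 0.9^8 = 57% | 19% | 46% |
| 20% | 4.8 | 1 − 0.8^8 = 83% | 50% | 87% |

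Without the completion condition, later withdrawal causes no loss.

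**Effect on precision.** The 95% half-width for one arm's mean is t(0.975, n−1) × s/√n. This is 0.836s for n = 8, 0.925s for n = 7 and 1.049s for n = 6, so widening is 11% at n = 7 and 26% at n = 6. If all three arms lose equally, the half-width for a pairwise difference in the ANOVA is t(0.975, 3(n−1)) × s√(2/n). This widens by 8% at n = 7 and 18% at n = 6.

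**Selection, for scale only.** Every input here is assumed: 10–20% non-completion, odds of leaving doubled or tripled per SD of log exposure, and between-patient CV of 30–50% (SD of log exposure √ln(1 + CV²) = 0.294 to 0.472). The mean log exposure of completers then shifts by −0.066 to −0.185 SD. The ratio of geometric means runs from exp(−0.066 × 0.294) = 0.98 to exp(−0.185 × 0.472) = 0.92, so completers' exposure is understated by about 2–8%. If leaving is unrelated to exposure, the shift is zero.

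**The case against.** The strongest reply is that the reach of the sentence is limited. It governs the statistical analyses, not the listings, plots and descriptive tables, so every dosed patient's profile can still be reported. That stands: the loss is to the ANOVA and not necessarily to the report.

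Second, a reader might infer that patients who stop dosing for intolerance are the ones removed. The protocol does not support that. Section 6.4 asks them to stay for scheduled evaluations, and section 4.4.4 requires treatment, not participation, to stop after a related serious adverse event. Such patients can complete the study and stay in the PK analysis. Only full withdrawal or loss to follow-up triggers exclusion.

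Third, a reader might infer harm to an exposure–safety comparison. None is planned; the safety analysis is descriptive.

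Fourth, section 10.3.3 leaves details to the statistical analysis plan. That could add evaluability rules, but it does not withdraw a population the protocol has already set.

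Finally, one might defend the condition by the synopsis, which promises to evaluate the effects of multiple dosing. No PK sample is scheduled at the second or third dose, so completion would add no PK data for that purpose. That mismatch needs its own clarification.

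**Conclusion.** The point holds for the inferential PK analysis. The completion condition has no stated rationale and can drop usable first-dose profiles on the basis of a later event.

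Where any patient leaves fully, the certain cost is precision. The 10–20% range behind the table is an assumption, and the rate relevant here excludes patients who stop treatment but stay in follow-up. Reading completion as week 48 is an inference from section 4.1 and the synopsis, since section 10.3.3 does not define it; the conclusion does not depend on it.

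It would go too far to say that exposure estimates will be biased. Bias requires a link between leaving and exposure, and the document allows neither that link nor its size to be established; the 2–8% is illustrative only. Because PK is a secondary objective in an exploratory study, this is a correction that should be made, but it does not threaten the primary safety objective.

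**What to change.** Replace the population sentence in section 10.3.3, and carry the same definition into the statistical analysis plan, along these lines:

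*The PK statistical analysis set comprises all patients who receive the first dose of DC-TAB and have sufficient post-dose concentrations to derive at least one PK parameter, regardless of later study completion. A profile is excluded only for a documented dosing or sampling error, decided before unblinding.*

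This costs one sentence in each document and needs no extra samples, visits or patients. Because the set rests on first-dose data, the sponsor should at the same time state what the synopsis means by evaluating the effects of multiple dosing on PK.
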